### Objectives {7}

The primary objective of this study is to assess whether therapeutic feeding with a simplified protocol results in 1) superior nutritional outcomes compared to no therapeutic feeding and 2) non-inferior nutritional outcomes compared to the WHZ and weight-based dosing regimen currently used in CMAM treatment, 2 months after diagnosis among children aged 6–59 months with MUAC ≥125 mm and WAZ <−3.

The secondary objective of this study is to assess whether therapeutic feeding with a simplified protocol results in (1) sustainably superior nutritional outcomes compared to no therapeutic feeding and (2) sustainably non-inferior nutritional status compared to the WHZ and weight-based dosing regimen currently used in CMAM treatment, 6 months after diagnosis among children aged 6–59 months with MUAC ≥125 mm and WAZ <−3.

Additional objectives include assessing whether the simplified protocol results in fewer children presenting negative outcomes compared to no treatment and non-inferior treatment outcomes compared to standard treatment.

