Treatment provided	None	1 sachet of RUTF/day	Depending on the WHZ score: • WHZ <−3: 200 kcal of RUTF/kg/day • WHZ between −3 and −2: 1 sachet of RUTF/day • WHZ ≥−2: no treatment
Recovery criteria from treatment	None	WAZ >−3 on 2 consecutive visits	WHZ ≥−2 on 2 consecutive visits

All other exit categories except for MUAC <125 mm or edema or died continue in the study unless the caregiver is not willing to do so. All children requiring inpatient-level care will be referred to the health center’s head nurse or doctor for them to prepare a formal referral of the patient to inpatient care.

Children will be classified in 5 different categories at the exit from the study: (1) finished 6-month follow-up, (2) developed MUAC <125 mm or edema during follow-up and was referred to routine treatment, (3) abandoned study, (4) lost-to-follow-up, (5) died. Abandoned will be defined as those who do not come back to study visits but who have been contacted to confirm the child is still alive. Lost-to-follow-up will be defined as those who do not come back to study visits and who have not been reached to confirm whether the child is still alive.

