### Outcomes {12}

Both primary and secondary outcomes will be reported for all 3 arms at both 2 (primary endpoint) and 6 months (secondary endpoint) post-enrolment. The primary outcome is the mean WAZ of children. WAZ has been shown to be strongly associated with mortality and thus acts as a proxy of the ultimate goal of reducing child mortality. Increase in WAZ can be both related to the increase in HAZ or WHZ, which is an added value as it enables appreciating and aggregating both outcomes that are positive. As a continuous measure, WAZ is well adapted to capture the response to treatment among the study population as it will more easily capture smaller benefits of treatment compared to categorical outcomes.

Secondary outcomes include (a) proportion of children with WAZ <−3, (b) mean MUAC of children, (c) mean WHZ and HAZ, (d) proportion of children with WHZ <−3 or HAZ <−3, (e) mean skinfold thickness measures and mean skinfold thickness per age percentile, (f) mean fat-free mass and fat mass, fat-free mass index and fat mass index, (g) mean hemoglobin measure, and (h) change in all these outcomes from enrolment to endpoint. In addition, the proportion of children exiting the study at any time point due to a MUAC <125 mm or edema or diseased or hospitalized will be reported across arms. Finally, treatment outcomes will be reported for the 2 treatment groups including the percent recovered, defaulted, non-response, transferred to inpatient care, and died. The study exit status will be reported for all 3 arms including completion of the 6-month follow-up, developed a MUAC <125mm or edema during the study, abandoned study, lost-to-follow-up, and died.

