### Sample size {14}

Based on previous work on a similar population and similar intervention [48] we assumed a similar response to treatment and a similar SD for WAZ. Thus, for looking at hypothesis 1, we set an objective of measuring a meaningful impact of the simplified treatment (compared to no treatment) at a difference of 0.4 *z*-scores in WAZ. For calculating the sample size, we applied (a) SD of 1.1 WAZ, (b) power of 80%, (c) probability of type 1 error of 2.5%, and (d) obtained a sample size of 146 per group. Accounting for not having measures for 30% of children (particularly in the control arm) at 2 months due to (a) defaulting, lost-to-follow-up, or death (10%) or (b) development of MUAC <125 mm or edema (20%), we estimated needing 209 children in both control and simplified treatment arms each.

For looking at hypothesis 2 we set an objective of measuring a meaningful non-inferiority margin of 0.2 *z*-scores in WAZ. For calculating the sample size, we applied (1) SD of 1.1 WAZ, (2) non-inferiority margin of 0.2, (3) power of 80%, and (4) probability of type 1 error of 2.5% and obtained a sample size of 475 per group. Accounting for not having measures for 20% of children at 2 months due to (a) defaulting, lost-to-follow-up, or death (10%) or (b) development of MUAC <125 mm or edema (10%), we need 594 children in simplified and standard treatment arms each.

To be able to explore both hypotheses, we need 209 children in the control arm and 594 children in both the simplified and standard treatment arms meaning a total of 1397 children.

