## Statistical methods

### Statistical methods for primary and secondary outcomes {20a}

In reporting the trial outcomes, we will follow the CONSORT 2010 statement for reporting parallel group randomized trials [50]. This will include reporting participant flow through the trial as per the CONSORT guidance [50]. All statistical analysis will be done using STATA® software or similar. Baseline characteristics will be reported by the study arm. Linear mixed models will be fitted to analyze the primary outcome and all continuous outcomes while logistic mixed-effects models will be fitted for binary or categorical outcomes. Random effects will include participants, study sites, and study teams. Adjustment for block randomization will be applied by means of random effects. Adjustment for confounders such as age and sex and outcome at enrolment will be included. To investigate effect modification, two-way interactions between intervention group and age group, sex, and degree of undernutrition (WHZ, WAZ and HAZ categories) will be assessed.

Anthropometric outcomes at 2 and 6 months post enrolment will be analyzed by adjusting for the exact number of days from enrolment to the measurement date. In addition, the treatment outcomes will be described for the 2 treatment groups, and the study exit status for all 3 study groups using count and percentage.

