### Methods in analysis to handle protocol non-adherence and any statistical methods to handle missing data {20c}

All analyses will be carried out in an all available case basis, i.e., all study participants will be included in the analysis. In case of missing outcome data at the primary and secondary endpoints of 2 and 6 months respectively, imputation will be performed using key variables such as age, sex, time since enrolment, randomization arm, treatment status, other anthropometry, and any other (previous or later) outcome measure data points. The primary analysis will apply a “de facto” principle [51] answering to the question of whether the treatment works in a real-life setting, and will thus analyze the data irrespective of degree of adherence to their treatment group. In addition, a “de jure” analysis will be performed to estimate the efficacy of the treatment in a best-case scenario, adjusting for the actual dose obtained, simulating a per-protocol analysis, as per the recommendations for non-inferiority analysis [52, 53]

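### The any-time deterioration outcome is set as a simple proportion with no allowance for unequal follow-up, so its between-arm difference depends on dropout

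*Protocol article*

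**What the plan says.** Objectives {7} of the protocol article lists, as an additional objective, whether the simplified protocol leaves "fewer children presenting negative outcomes compared to no treatment". Outcomes {12} gives the matching measure, placed after the lettered secondary outcomes: "the proportion of children exiting the study at any time point due to a MUAC <125 mm or edema or diseased or hospitalized", to be reported across arms.

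Statistical methods {20a} states that "logistic mixed-effects models will be fitted for binary or categorical outcomes" and that exit status is described: "the study exit status for all 3 study groups using count and percentage". The one adjustment for follow-up time concerns other variables: "Anthropometric outcomes at 2 and 6 months post enrolment will be analyzed by adjusting for the exact number of days from enrolment".

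Intervention description {11a} puts each child in one of five study-exit classes. Abandoned and lost-to-follow-up are separate from MUAC <125 mm or edema. An abandoned child has only been confirmed alive, and a lost child has not been reached at all.

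The section on non-adherence and missing data {20c} keeps all participants in the analysis and adds: "In case of missing outcome data at the primary and secondary endpoints of 2 and 6 months respectively, imputation will be performed".

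**The concern.** This outcome is the trial's direct evidence on whether feeding prevents deterioration in children who would otherwise go untreated. A child who stops attending at week 4 did not exit for a listed reason. Taken literally, that child enters the denominator for the full 24 weeks and never the numerator, although nutritional status after week 4 is unknown. Exit class is recorded for every child, so nothing appears missing and the imputation rule may never be triggered.

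The proportion then estimates who was seen to deteriorate before leaving. The objective asks who deteriorates within the period. The absolute risks are understated in every arm, and the difference between arms takes on whatever dropout pattern occurs. In an open-label trial with an unfed control arm, that pattern cannot be predicted.

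**Working it through.** **Planning figures.** Sample size {14} gives no figure for this outcome, but its loss allowances supply the inputs. They reproduce:
- Superiority: 146/(1 − 0.30) = 208.6, so 209.
- Non-inferiority: 475/(1 − 0.20) = 593.75, so 594.
- Total: 209 + 2 × 594 = 1397.

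**Inputs at 2 months (Sample size {14}).** Deterioration *d* is 20% in the superiority calculation (taken here as the control rate) and 10% in the non-inferiority calculation (taken as the simplified rate). Defaulting, loss or death *l* is 10% in both.

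**Assumptions.** Hazards are constant to 6 months, loss is independent of deterioration, and all of *l* is loss of observation.

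**Formulas**, for *k* two-month periods:
- Crude proportion, leavers as non-events: d/(d + l) × [1 − (1 − d − l)^k]
- Risk with leavers censored: 1 − (1 − d − l)^(k·d/(d + l))

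**At 6 months (k = 3), 10% loss per arm:**
- Control: crude 2/3 × (1 − 0.7³) = 43.8%; censored 1 − 0.7² = 51.0%.
- Simplified: crude 1/2 × (1 − 0.8³) = 24.4%; censored 1 − 0.8^1.5 = 28.4%.
- Difference: 19.4 against 22.6 points, so 1 − 19.4/22.6 = 14% attenuation.
- Odds ratio, simplified to control: 0.41 against 0.38.
- Power of the crude comparison with 209 and 594 children: about 99.9%.

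**At 2 months (k = 1):** the crude difference is 10.0 points. Censored risks are 21.2% and 10.6%, a difference of 10.6 points. Attenuation is about 6%.

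**Sensitivity to loss at 6 months.** The loss figures other than 10%/10% are assumptions.

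| 2-month loss, control / simplified | Crude difference | Censored difference | Effect |
|---|---|---|---|
| 10% / 10% | 19.4 | 22.6 | 14% smaller |
| 5% / 5% | 20.5 | 22.1 | 7% smaller |
| 20% / 10% | 14.8 | 25.1 | 41% smaller |
| 10% / 20% | 21.9 | 21.0 | 4% larger |
| 5% / 15% | 23.1 | 20.7 | 12% larger |

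**Without extending the hazards.** If the 6-month risks are 20% and 10%, with 10% loss per arm over the whole 6 months, the difference is 9.5 against 10.0 points. The odds ratio is 0.45 against 0.44, and power is 93% against 94%.

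**The case against.** No sentence in the article says that abandoned or lost children count as not deteriorated, and no denominator is given. The imputation rule could be meant to cover this outcome, and the general logistic sentence might not apply to it. The denominator and censoring rule of an additional outcome could also sit in an analysis plan that is not shown. This stands as a limit on certainty: non-event coding is the natural reading, not a stated rule. It does not remove the point, because the article itself fixes the summary measure, the available models and the analysis set, and restricts the time adjustment to anthropometry.

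The size can fairly be called overstated. The 10% allowance includes deaths. It also includes defaulters, who under Intervention description {11a} continue in the study unless the caregiver declines. The 5% row is therefore plausible, and the extension from 2 to 6 months is assumed.

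A reader might infer that the difference is certain to be attenuated. The documents do not support that: the planned loss is the same 10% in both calculations, and the last two rows of the table reverse the sign. The higher missingness expected in control comes from MUAC or edema exits, which are the event itself. The 41% row therefore rests on an assumed loss figure alone.

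A reader might also infer that non-event coding helps a non-inferiority claim. No non-inferiority test or margin is planned for this composite. The objective on negative outcomes concerns the comparison with no treatment.

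**Conclusion.** The point holds in a limited form. The outcome is a plain any-time proportion with no allowance for unequal follow-up, and the most natural reading counts early leavers as non-events. The proportions then understate deterioration in each arm, and the simplified-versus-control difference depends on dropout. With equal loss, attenuation at 6 months is about 14% if the full 10% is true loss and hazards are constant, and about 7% if only 5% is. At 2 months it is about 6%. Higher control loss enlarges it, and sufficiently higher loss in the simplified arm turns it into exaggeration.

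The odds ratio and power change little under equal loss, and mean WAZ at 2 months is unaffected. This is a cheap improvement, not a threat to the trial's main conclusions.

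**What to change.** In Outcomes {12} and Statistical methods {20a}, define the outcome as time from enrolment to the first listed event. Censor children who abandon or are lost at their last attended visit. Fit a discrete-time complementary log-log model, which suits fortnightly and monthly visits, or a Cox model, with the same site effect and covariates. Report cumulative incidence by arm at 8 and 24 weeks with confidence intervals. Keep the exit-status counts and percentages as description.

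Reconcile the event list at the same time. Outcomes {12} treats hospitalization as a reason for exiting the study, while Intervention description {11a} keeps transferred children in the study and has no such exit class. Outcomes {12} should also make clear whether the term next to hospitalization means illness or death, because that decides whether death is an event or a competing event.

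The cost is wording and analysis code. MUAC and edema are already measured at every visit, so no new data are needed, and the change can be made before the allocation code is released. The downside is that the method assumes dropout is non-informative given the covariates. That is weaker than assuming that no child deteriorates after leaving.

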### Participant timeline {13}

Study participants will be followed up fortnightly for the first 12 weeks and then monthly until 6 months. Figure 1 illustrates the visit schedule for any study participant and Table 2 presents the timing and frequency of different study procedures.

**Fig. 1 Fig1:**
[figure not shown]
Timeline of study visits for all participants and intervention for participants in the simplified and standard arms

**Table 2 Tab2:** Timing and frequency of different study procedures for children enrolled in the ComPAS low-WAZ RCT in Mali

Procedure	Week prior to enrolment	Enrolment	At each fortnightly and monthly visit	At 2 months and 6 months
Pre-screening for eligibility	X			
Eligibility		X		
Consent		X		
Socio-economic questionnaire		X		
Anthropometry (weight, height, MUAC)		X	X	X
Clinical exam		X	X	X
Body composition		X		X
Hemoglobin		X		X

### Sample size {14}

Based on previous work on a similar population and similar intervention [48] we assumed a similar response to treatment and a similar SD for WAZ. Thus, for looking at hypothesis 1, we set an objective of measuring a meaningful impact of the simplified treatment (compared to no treatment) at a difference of 0.4 *z*-scores in WAZ. For calculating the sample size, we applied (a) SD of 1.1 WAZ, (b) power of 80%, (c) probability of type 1 error of 2.5%, and (d) obtained a sample size of 146 per group. Accounting for not having measures for 30% of children (particularly in the control arm) at 2 months due to (a) defaulting, lost-to-follow-up, or death (10%) or (b) development of MUAC <125 mm or edema (20%), we estimated needing 209 children in both control and simplified treatment arms each.

For looking at hypothesis 2 we set an objective of measuring a meaningful non-inferiority margin of 0.2 *z*-scores in WAZ. For calculating the sample size, we applied (1) SD of 1.1 WAZ, (2) non-inferiority margin of 0.2, (3) power of 80%, and (4) probability of type 1 error of 2.5% and obtained a sample size of 475 per group. Accounting for not having measures for 20% of children at 2 months due to (a) defaulting, lost-to-follow-up, or death (10%) or (b) development of MUAC <125 mm or edema (10%), we need 594 children in simplified and standard treatment arms each.

To be able to explore both hypotheses, we need 209 children in the control arm and 594 children in both the simplified and standard treatment arms meaning a total of 1397 children.

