### Trial design {8}

The study is a parallel group individually randomized controlled trial with three study arms allocated unevenly to test both a superiority and a non-inferiority hypothesis: 209 children will be recruited for the control arm (only involved in the superiority hypothesis testing) and 594 children in each intervention group.

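### The same stated 2.5% type 1 error is two-sided in the superiority sample size and one-sided in the non-inferiority one, and the 80% superiority power is for equal arms that the trial does not have

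*Protocol article*

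**What the plan says.** Under Sample size {14}, the protocol article sizes two hypotheses on mean WAZ at 2 months.

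- **Hypothesis 1, simplified treatment superior to no treatment.** The target is set "at a difference of 0.4 *z*-scores in WAZ". The other inputs are "a) SD of 1.1 WAZ, (b) power of 80"%, then "c) probability of type 1 error of 2.5%, and (d) obtained a sample size of 146 per group". Loss is allowed for: "Accounting for not having measures for 30% of children (particularly in the control arm) at 2 months". The result is "we estimated needing 209 children in both control and simplified treatment arms each".
- **Hypothesis 2, simplified treatment non-inferior to standard treatment.** The inputs are "1) SD of 1.1 WAZ, (2) non-inferiority margin of 0.2, (3) power of 80"%, then "4) probability of type 1 error of 2.5% and obtained a sample size of 475 per group". With a 20% allowance for missing measures this becomes 594 per arm.

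The section then takes the larger number for the shared simplified arm: 209 control, 594 simplified and 594 standard, 1397 in total. Trial design {8} describes "three study arms allocated unevenly to test both a superiority and a non-inferiority hypothesis". Neither section says whether 2.5% is one-sided or two-sided, and neither restates the power of hypothesis 1 for 209 against 594.

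**The concern.** The two calculations share SD, power and stated error rate. They differ only in the distance to be resolved: 0.4 for superiority and 0.2 for the margin. Halving that distance should multiply the sample size by four if everything else is the same. Four times 146 is 584, not 475, and a quarter of 475 is about 119, not 146. The gap is too large for rounding and suggests that the error rate is used in two senses.

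Two things depend on this. First, both hypotheses make up the primary objective, and non-inferiority is decided by where a confidence bound falls against 0.2 WAZ. A reader should be able to tell from the sample size which level each comparison was designed for. Second, the only power figure given for hypothesis 1 describes two arms of 209, which is not the comparison that the trial will make.

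**Working it through.** **Inputs, all from Sample size {14}.** SD 1.1; difference 0.4 (hypothesis 1); margin 0.2 with true difference taken as 0 (hypothesis 2); power 80%; type 1 error 2.5%; loss 30% and 20%; enrolment 209, 594 and 594.

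**Sample size per group.** The normal-theory formula is n = 2(z_α + z_β)² SD² / d², with z_β = 0.8416. For 2.5% one-sided, z_α = 1.9600 and (z_α + z_β)² = 7.849. For 2.5% two-sided, which is 1.25% per side, z_α = 2.2414 and (z_α + z_β)² = 9.505. The t-based column is the smallest whole n that reaches 80% under the noncentral t distribution.

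| Hypothesis | Reading of 2.5% | Normal formula | t-based | Protocol |
|---|---|---|---|---|
| 1 (d = 0.4) | two-sided | 2 × 9.505 × 1.21 / 0.16 = 143.8, so 144 | 146 | **146** |
| 1 (d = 0.4) | one-sided | 2 × 7.849 × 1.21 / 0.16 = 118.7, so 119 | 120 | |
| 2 (d = 0.2) | one-sided | 2 × 7.849 × 1.21 / 0.04 = 474.9, so 475 | 476 | **475** |
| 2 (d = 0.2) | two-sided | 2 × 9.505 × 1.21 / 0.04 = 575.1, so 576 | 577 | |

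Both protocol figures are reproduced, but under different readings. The choice between the normal and t formulas moves n by one or two children. The choice of sidedness moves it by about 26 per group for hypothesis 1 (146 against 120) and about 100 for hypothesis 2 (576 against 475). No single reading gives both figures.

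**Loss allowance.** 146 / 0.7 = 208.6, so 209. 475 / 0.8 = 593.75, so 594. 209 + 594 + 594 = 1397. All three match, so both readings are carried into the total.

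**Power of hypothesis 1.** Power = Φ(d / SE − z_α), with SE = 1.1 × √(1/n₁ + 1/n₂). Evaluable controls are 209 × 0.7 = 146. The evaluable simplified arm is 594 × 0.7 = 416 or 594 × 0.8 = 475, because the section applies 30% loss to that arm in one calculation and 20% in the other.

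| Evaluable, control against simplified | SE | d / SE | Power, two-sided 2.5% | Power, one-sided 2.5% |
|---|---|---|---|---|
| 146 against 146 | 0.1287 | 3.107 | 80.7% | 87.4% |
| 146 against 416 | 0.1058 | 3.780 | 93.8% | 96.6% |
| 146 against 475 | 0.1041 | 3.843 | 94.5% | 97.0% |

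The first row at two-sided 2.5% is the protocol's own 80% (80.3% with the t distribution). The planned arms give about 94%, or about 97% one-sided.

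**Power of hypothesis 2.** With 475 against 475, SE = 0.0714 and 0.2 / SE = 2.802. At one-sided 2.5%, power is Φ(2.802 − 1.960) = 80.0%, as stated. At 1.25% one-sided it would be Φ(2.802 − 2.241) = 71.2%.

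**The case against.** The strongest reply is that nothing printed is wrong. Every figure can be reproduced, and a two-sided superiority test paired with a one-sided non-inferiority test is ordinary practice. A coherent scheme also fits: 5% overall, divided equally between two hypotheses, with the 2.5% spent two-sided on the first and one-sided on the second. Sizing each comparison separately and giving the shared arm the larger number is conservative, and the article nowhere claims that 209 against 594 has 80% power. The confidence level for the analysis may also properly be left to an analysis plan.

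Much of this stands. The mixed pairing is defensible, and the mismatch in superiority power is on the safe side. What remains is that the article uses one expression for two different error rates without saying so. An analysis plan can choose a convention, but it cannot make both printed figures follow from one meaning of 2.5%.

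Three stronger readings are tempting, and the documents do not support them.

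- **Non-inferiority has only 71% power.** That holds only if hypothesis 2 is tested at 1.25% one-sided. No section says this, and the printed 475 shows that it was not the design assumption.
- **The error rate was halved for multiplicity in one hypothesis and not in the other.** The figures do not show why hypothesis 1 uses 1.25% per side. The equal split described above explains them just as well.
- **The control arm is wastefully large.** Fewer controls would have reached 80%, but Trial status reports recruitment completed in October 2023, so this has no practical consequence.

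**Conclusion.** The point holds as a correction to the sample-size statement and does not show an underpowered trial. With SD 1.1 and 80% power, 146 per group requires two-sided 2.5% and 475 per group requires one-sided 2.5%. On the levels that the figures imply, non-inferiority has its stated 80%. Superiority has about 94% with the planned arms, against a stated 80% that belongs to equal arms of 209.

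These powers assume a plain two-sample comparison with the protocol's SD, a true difference of 0.4 for hypothesis 1 and of zero for hypothesis 2, and 20% to 30% loss in the simplified arm. The planned mixed model adjusts for the outcome at enrolment and missing outcomes are to be imputed, so actual power will differ and the last digit should not be relied on. The disagreement between the two readings of 2.5% does not depend on the analysis model.

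**What to change.** In Sample size {14}, do one of the following.

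1. Keep both figures and state the level behind each: two-sided 2.5% (a 97.5% confidence interval) for hypothesis 1, and one-sided 2.5% (the relevant bound of a two-sided 95% confidence interval) for hypothesis 2.
2. Adopt one convention and correct the figure that no longer matches. With one-sided 2.5% throughout, the requirement for hypothesis 1 becomes 119 to 120 per group and 475 stands. With two-sided 2.5% throughout, the requirement for hypothesis 2 becomes 576 to 577, and its power at 475 must be restated as about 71%.

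In either case, restate the power of hypothesis 1 for 146 against 416 to 475 evaluable children: about 94% at two-sided 2.5%, or about 97% if one-sided 2.5% is adopted.

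The cost is a few sentences. No change in enrolment is needed, and no fixed testing order has to be introduced. The analysis level should be confirmed to match before the intervention codes are released to the investigators, so that it is not chosen with results in view.
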